# PATIENT AND PUBLIC INVOLVEMENT (PPI)

The ReIMAGINE project includes a work strand which focusses solely on PPI engagement. This work strand is led by [name] a prostate cancer survivor, and the ReIMAGINE PPI representative and [name] [name].

The clinical investigators have discussed the design of the study including number of visits and outcome measures, with [name]. There will be PPI representation on the TSC. All patient facing documents will be reviewed by the PPI representative and he will be called upon to contribute to the reporting of the study report and dissemination of research findings.

# FUNDING AND SUPPLY OF EQUIPMENT

The study is jointly funded by the Medical Research Council (£5.18M GBP) and Cancer Research UK (£1M GBP) on grant award MR/R014043/1, funding letter dated 19 February 2018. Grant funded clinical trial practitioners and tissue technicians will undertake the majority of the research activity resulting in minimal impact to NHS resources.

The study funding has been reviewed by the UCL/UCLH Joint Research Office, and deemed sufficient to cover the requirements of the study. NHS treatment costs will be supported via standard NHS commissioning routes and service support activity via Local Clinical Research Networks.

The management of the research will be covered by UCL insurance for negligent harm.

UCL insurance provides cover for negligent harm arising from the design of the research.

The NHS indemnity scheme will apply for negligent harm arising from the conduct of the research.

The study is supported by multiple external partners by way of in-kind contributions to biomarker analysis, imaging analysis and database hosting. The ReIMAGINE consortium will share anonymised MRI images and biological samples with multiple external partners, who will analyse these samples against their biomarker(s) or imaging software. Each external partner will sign the consortium agreement which details the in-kind contributions they will make to the consortium.

# DATA HANDLING AND MANAGEMENT

ReIMAGINE Prostate Cancer Risk will have two separately managed and hosted databases to handle identifiable and pseudonymised data.

**Pseudonymised data**

Data collected in the study will include baseline clinical and demographic data, detailed histology and imaging. Such patient data shall be accessed, with full informed consent, using hospital-specific software systems and paper medical notes.

Source data will be entered onto the study database from each recruiting centre using an electronic case report form (eCRF). The Chief Investigator (CI) is responsible for reviewing all information collected on patients enrolled in the study for completeness and accuracy. The delegation log will identify and name all those personnel with responsibility for both data collection and handling and will include further information on the access rights of each delegate to the data warehouse.

The data warehouses, which are hosted and managed securely by UCL and Philips in the EU, will be safeguarded against unauthorised access with established security procedures. Additional maintenance will include regular back-ups and upkeep of related software files. Patients will not be identifiable in the study database but will be identified by unique patient ID numbers assigned at the point of recruitment into the study.

The identification, screening and enrolment logs which will link participant identifiable data to the pseudonymised patient ID number will also be held locally by each study site. Physical copies of these logs will be stored in locked filing cabinets and electronic versions held on password protected NHS Trust computers.

It is the responsibility of each study site to maintain a file of essential study documentation (Investigator Site File), and to maintain their file of essential study documentation on site during the study and thereafter at the designated archive facility.

The Chief Investigator, Philips and delegates are responsible for the daily management of the data warehouse. The following guidelines will be strictly adhered to:

Any patient data stored on the software system hosted by Philips will be pseudonymised.

All anonymised data will be password-protected, with differing levels of access agreed for each delegate prior to study initiation.

Database management methods will be documented according to scientific method standards which will contain enough detail to theoretically allow independent researchers to repeat the experiment. The data warehouse software’s provided by UCL and Philips include various features to ensure data quality including maintenance of audit trail, allowance of custom validation on all data and the ability for users to raise data query requests and search facilities to identify missing data or validation failure.

Copies of the final locked database with documentation of variables, coding and data cleaning before statistical analysis will be stored by the database manager. The database manager will run queries to extract the data. The data will be extracted in tables and provided to the researchers in excel and CVS format. Data documentation will be supported by the Statistical Master File which will include: details of statistician consistency checks; documentation of import of statistical data; statistical package; location of statistical program files. All statistical analysis programs will be fully documented.

The ReIMAGINE consortium includes data sharing agreements with a number of academic and commercial partners. All data released from the consortium will appear in an anonymised format. Access to the shared data repository will be restricted and controlled by the database team based at University College London in partnership with King’s College London. The shared data repository infrastructure will be provided by UCL and Philips. The Philips team will have limited access to data as agreed in the data sharing contract signed by the ReIMAGINE lead institution. All commercial and academic partners involved in the ReIMAGINE consortium have signed and agreed specific data sharing contracts – all based on pseudonymised data.

After completion of the ReIMAGINE study, the data warehouse (hosted by Philips) will be transferred securely from Philips to University College London for on-going analysis of secondary outcomes. Data transfer will occur using end to end encryption.

All data will be handled in accordance with the Data Protection Act 2018 and General Data Protection Guidance (2018).

**Identifiable Data**

Patients will be asked to give their consent to provide identifiable information such as their name, address, date of birth and NHS number at point of entry to the study. This information will be stored securely by University College London in the United Kingdom. This identifiable data will be used to collect healthcare information on men from national records, such as the Office for National Statistics, NHS Digital, Public Health England, and other applicable NHS information system, or national databases. This process will be clearly explained to patients in the patient information sheet provided prior to consent. The Chief Investigator agrees to hold such identifiable information, alongside the assigned unique patient ID number, securely on servers hosted and maintained by UCL. This server is fire-wall protected and provides auto failover redundancy in the event of hardware failure. The data backup schedule follows standard full backups. The physical location of this server is protected by CCTV and security door access. All records will be retained by the CI according to the International Conference on Harmonisation (ICH) or local regulations; all study documentation will be retained for 20 years after the study end date unless advised otherwise by the sponsor.

Access to the identifiable patient data held securely at University College London will be restricted to named personnel only. Only the data controller and named members of the data management team will be granted access to the identifiable patient data held securely at University College London.

# MATERIAL/SAMPLE STORAGE

In the study blood, urine and prostate tissue cores will be collected from patients in accordance with the patient consent form and patient information sheet and shall include all tissue samples or other biological materials and any derivatives, portions, progeny or improvements as well as all patient information and documentation supplied in relation to them. Samples will be processed, stored and disposed in accordance with all applicable legal and regulatory requirements, including the Human Tissue Act 2004 and any amendments thereafter.

Biological samples will be stored under HTA licence 12055 and shipped periodically to academic and commercial partners in the EU, North America and Australia for analyses. These partners will be part of the ReIMAGINE consortium and have appropriate material transfer agreements (MTA’s) in place before shipment of any samples from the central laboratory at UCL. A list of partners is detailed in appendix III.

Access to any human samples requires a request and approval by the biological research group that will maintain scientific rigour and prioritisation of material. Samples are not to be processed and/or transferred other than in accordance with the patients’ consent.  After ethics approval for the study has expired, the blood, urine and tissue samples will be disposed of in accordance with the Human Tissue Act 2004 and any amendments thereto or transferred to a licensed tissue bank.

## Blood Sample Collection

- Blood samples will be collected by trial employed clinical trial practitioner in advance or on the day a MRI guided biopsy is taken. This could be in a dedicated clinic, on the ward or intraoperatively during the biopsy procedure (when a cannula is already in situ). The patients will receive a copy of their signed consent form and the Patient Information Sheet.
- A minimum volume of 50ml will be requested, with a maximum volume of 100ml in men who are able and willing to provide this.
- The blood samples will be processed by a CTP or a Technician using the hospital’s laboratory facilities. For detailed information on preparation, storage and shipment of blood samples please refer to the ReIMAGINE Prostate Cancer Risk Laboratory Manual.
- Once the whole blood has been processed, it will be logged into FreezerPro database. No patient identifiable information will be entered onto the database and all patient information will be pseudonymised. All samples will be stored temporarily onsite at -80C. At regular intervals the samples will be sent using a courier to:

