Our industry partners are developing algorithms to detect at high-resolution tumour DNA in plasma that will be evaluated for associations with risk of progression. By integrating with matched tumour multi-region sequencing data and complementing with high-coverage targeted NGS performed separately on the extracted plasma DNA, we aim to identify independent predictors of progression detected in circulation prior to biopsy and track sub-clonal relapse in follow-up samples.

This protocol has been informed, developed and approved in collaboration with patient and public involvement initiatives occurring in parallel with preparation of this submission. Additional experience is based on investigators’ experience in the PROMIS trial which successfully recruited on time and led to a change in pathway, has been incorporated into this protocol ([name] H *et al.* Lancet 2017). PRECISION, an international, multi-centre randomised study that compared an mpMRI based pathway with the standard of care (TRUS-Biopsy) showed that the MRI-based pathway was superior in terms of the proportion of men with clinically significant disease that were identified, the reduction in over-diagnosis that occurred and the observation that less harm was experienced by those randomised to mpMRI. Our previous PROGENY study also showed that the principle of imaging characterisation followed by diagnostic and research biopsy samples had a high uptake by patients with 80% of men approached agreeing to consent to the study [Linch et al, 2017/18, Annals of Oncology].

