# STUDY DESIGN

ReIMAGINE Prostate Cancer Risk is a multi-centre, prospective, observational, longitudinal cohort study of men referred to secondary care with a suspicion of prostate cancer or men who are undergoing further tests for prostate cancer staging assessment. Men with a serum PSA level of 20ng/ml or less, whose mpMRI scan has been scored as PIRADS/LIKERT score 3, 4 or 5, and who have been advised and accepted the need for a targeted and systematic prostate biopsy will be invited to enrol.

Men will be recruited across a number of high-volume NHS centres which already have an mpMRI based diagnostic pathway. The study has an initial cross-sectional component where consenting men will be asked to donate blood, urine, imaging files and prostate biopsy tissue for biomarker analysis before or at the time of their standard of care prostate biopsy.

After collection of the cross-sectional biological samples within ReIMAGINE, men will revert to NHS standard of care, attending a routine outpatient appointment for the results of their prostate biopsy outside of the trial setting. Although there are no further planned study visits all men will be consented for healthcare data linkage to measure long-term outcomes including cancer progression, development of metastases and mortality for the longitudinal component of the study.

The ReIMAGINE team aim to recruit 1,000 men with a PIRADs/LIKERT score 3, 4 or 5 who are undergoing an MRI-directed prostate biopsy. Of these 1,000 biopsies, we anticipate that 60% will have any cancer detected on histology (3+3 or greater) giving approximately 400 cases of clinically significant cancer (Gleason 7 or more).

After 12 months of accrual to the study an interim review will be performed by the ReIMAGINE scientific advisory board *(see appendix I for SAB membership)* who will review both accrual rates and cancer incidence with the remit of reviewing and advising on the final recruitment target.

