# STUDY SCHEDULE

## Screening and Registration

Potential participants will be identified in a routine secondary care setting of the participating NHS sites by their clinical care team or ReIMAGINE funded staff. Participants may be identified at the point of referral to the hospital, within urology cancer clinics or by other means such as waiting lists or review of case records of the same NHS sites.

First approach of potential participants will predominantly occur via telephone and/or invitation letter conducted or sent by a ReIMAGINE staff member (clinical trials practitioner) following receipt and review of a primary care referral to the recruiting site. As some recruiting sites run a “one-stop” prostate cancer clinic, whereby men are biopsied on the same day as their MRI, the study protocol will include the option to send out a PIS to potential participants and call them to explain the study and discuss any questions they may have, following the clinical team having already explained the clinical standard pathway. As the time window between the MRI (which has to be reported to confirm eligibility) and biopsy (which can only be performed after blood and urine sample collection) is minimal approach by telephone is key to accrual.

If approached via telephone potential participants will be asked for their willingness to receive a patient information sheet (post/email) which will be sent in advance of their clinical appointment. All participants considered for recruitment onto the ReIMAGINE study will be recorded on the study participant screening log. To ensure completeness of data, any patient who receives a patient information sheet for the ReIMAGINE study- either at a face to face consultation, or through the postal service or email- will be included on the study participant screening log.

Consent will also be discussed over the phone and affirmation will be noted both on the eCRF and in medical records (electronic or paper), and on the day that the participant attends clinic for the first visit, wet signature will be obtained, to substantiate affirmation.

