***Demographic and general measurements***

- Medical history
- Demographics
- Family History
- Ethnicity
- Age
- Co-Morbidities
- Medication use

All consented patients who are deemed eligible will have already been advised and/or have a scheduled visit for a prostate biopsy on clinical grounds as standard care. On the day of consent or at the time of the scheduled prostate biopsy participants will have the below interventions:

- Donation of blood will be drawn from men, either via a trained phlebotomist or from the cannula already in situ in preparation for their prostate biopsy.
- Donation of urine. Provided by participant in advance of prostate biopsy.
- Up to three additional biopsy cores will be taken at the time of the standard of care biopsy. Two cores will be taken from the radiologically guided area of suspicion and one control sample from the contralateral non-suspicious area.

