**Long term healthcare data linkage**

The study will obtain informed consent from participants to collect long term healthcare information from national records, such as the Office for National Statistics, NHS Digital, Public Health England, and/or other applicable NHS information systems, or national databases. No further visits will be required for this activity, but permission will be obtained to receive and hold this information. The research team will collect this healthcare information up to three years after last patient last visit (LPLV) and further funding will be sought to collect this longer term (until death time point should funding be successful).

**Figure 2:** ReIMAGINE Prostate Cancer Risk Trial Flow Diagram

*
[figure not shown]
*

** Blood and Urine collection will always occur before the prostate biopsy is performed but may not always be on the same day as the biopsy procedure.*

**Table 1:** Schedule of Assessments

| **Visit** | **Screening & Registration** | **Visit 1*** | **Non-Visit** | **In direct collection** |
| --- | --- | --- | --- | --- |
| Timing of Visit | Day -1 | Day 1 | 3-6 Weeks | n/a |
| Registration | X |  |  |  |
| Medical History | X |  |  |  |
| Eligibility confirmation | X | X |  |  |
| Informed Consent |  | X |  |  |
| PSA | X |  |  |  |
| Research Blood |  | X |  |  |
| Research urine |  | X |  |  |
| Targeted biopsy |  | X |  |  |
| Biopsy results |  |  | X |  |
| FFPE tissue block and H&E slide collection |  |  | X |  |
| Adverse Events review |  | X |  |  |
| Concomitant Medication review (if applicable) | X |  |  |  |
| Healthcare data linkage |  |  |  | X |

** Blood and Urine collection will always occur before the prostate biopsy is performed but may not always be on the same day as the biopsy procedure.*

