## Urine sample collection

- Urine samples will be collected by trial employed clinical trial practitioner in advance or on the day a MRI guided biopsy is taken. This could be in a dedicated clinic or on the ward but will always occur in advance of the biopsy.
- Urine samples will be provided by participants into urine collection bottles and processed according to ReIMAGINE Prostate Cancer Risk Lab manual.
- The samples will be logged into the FreezerPro database and stored temporarily at the collection sites.
- At the regular intervals the samples will be shipped using a courier to:

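### Section 13.1 lets research blood be drawn during the biopsy procedure, against the protocol's own rule that blood comes first, so some plasma samples could follow the first needle pass unflagged

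*Protocol*

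**What the plan says.** The protocol sets the timing of the research blood draw in several places.

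- **Section 13.1, Blood Sample Collection.** Blood may be taken in advance or on the day of the biopsy, in a dedicated clinic, "on the ward or intraoperatively during the biopsy procedure (when a cannula is already in situ"). No order relative to the first needle pass is given.
- **Section 4, Study Design.** Blood, urine, imaging files and tissue are donated, as one list, "before or at the time of their standard of care prostate biopsy".
- **Section 5.1, Screening and Registration.** The one-stop clinic text refers to "biopsy (which can only be performed after blood and urine sample collection").
- **Section 5.1, note to Figure 2 and Table 1.** "Blood and Urine collection will always occur before the prostate biopsy is performed".
- **Section 5.1, Visit 1.** Blood comes from a phlebotomist or "from the cannula already in situ in preparation for their prostate biopsy". The risk table in Section 15 describes the cannula in the same way.
- **Section 13.2, Urine sample collection.** Urine may be collected in clinic or on the ward, "but will always occur in advance of the biopsy". Section 13.1 has no matching clause for blood.
- **Section 2, Background and Rationale.** For plasma tumour DNA, the aim is to "identify independent predictors of progression detected in circulation prior to biopsy".

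Section 5.2 requires a deviation form for shortfalls in blood volume, urine volume or number of cores. Timing is not among its triggers.

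**The concern.** A draw made during the biopsy procedure is not one that always precedes the biopsy. Someone at a site who reads Sections 13.1 and 13.2 together could reasonably conclude that the strict rule covers urine only.

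At stake is what the plasma measurement represents. Section 2 ties the tumour-DNA aim to what is in the circulation before biopsy. A sample taken after needles have entered the gland falls outside that description, however large or small the biological effect. If needling releases DNA or protein into blood, which is an assumption the protocol neither states nor quantifies, mixing the two kinds of sample would add noise to real markers. If the release were greater in men with tumour in the sampled area, it could lend apparent signal to a marker that has none. Samples are banked and shipped to partners, so a draw order that is not recorded at the time may be impossible to recover.

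**Working it through.** **1. The texts side by side**

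| Place | Is a draw after the first needle pass allowed? |
|---|---|
| Section 2, plasma aim | No, the aim is worded as pre-biopsy |
| Section 4 | Not excluded (before or at the time of biopsy) |
| Section 5.1, one-stop clinic text | No |
| Section 5.1, note to Figure 2 and Table 1 | No |
| Section 5.1, Visit 1; Section 15 | Not addressed; the wording fits a pre-needle draw |
| Section 13.1 | Not excluded (during the procedure) |
| Section 13.2 (urine only) | No |

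The same post-needle sample therefore complies with Section 13.1 and breaches Section 5.1.

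**2. Would anything reveal it?** Table 1 places research blood and targeted biopsy in the same Visit 1 column, Day 1, with no order. Section 5.2 triggers a form on amounts only. Section 17 defines deviations generally and says that they need not be reported to the sponsor. The protocol text names no draw time or first-pass time to record. The eCRF and the Laboratory Manual are not at hand and may contain these.

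**3. Possible size (assumed inputs).** The plan has no figure of its own to reproduce. From Section 9: 396 men with clinically significant cancer and 604 without. Assumed: a share *p* of draws is post-needle, unrelated to case status, with *p* = 10%, 25% or 50%. Markers are normal with SD 1 and mean difference *d* between cases and non-cases. Post-needle draws shift by *a* in cases and *b* in others, with extra noise of SD *t*. Then

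AUC = (1−p)²·Φ(d/√2) + p(1−p)·[Φ((d+a)/√(2+t²)) + Φ((d−b)/√(2+t²))] + p²·Φ((d+a−b)/√(2+2t²)).

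*Real marker, true AUC 0.75* (d = 0.954, a = b = 1, t = 1). The terms are 0.75, 0.870 + 0.489 = 1.360, and 0.683.
- p = 10%: 0.81×0.75 + 0.09×1.360 + 0.01×0.683 = 0.737
- p = 25%: 0.5625×0.75 + 0.1875×1.360 + 0.0625×0.683 = 0.720
- p = 50%: 0.25×0.75 + 0.25×1.360 + 0.25×0.683 = 0.698

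*Null marker, true AUC 0.50* (d = 0, a = 1, b = 0.5, t = 0). The terms are 0.50, 0.760 + 0.362 = 1.122, and 0.638.
- p = 10%: 0.405 + 0.101 + 0.006 = 0.512
- p = 25%: 0.281 + 0.210 + 0.040 = 0.532
- p = 50%: 0.125 + 0.281 + 0.160 = 0.565

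*Null marker, smaller shifts* (a = 0.35, b = 0.25, t = 0): 0.503, 0.507 and 0.514.

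*Precision at AUC 0.50* (Hanley-McNeil; both Q terms equal 1/3):
SE = √{[0.25 + (395 + 603)×(1/3 − 0.25)] / (396×604)} = √(83.42 / 239,184) = 0.0187. The 95% half-width is 1.96×0.0187 = 0.037.

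Under the larger shifts the excess over 0.50 is 0.012, 0.032 and 0.065. Only the last exceeds 0.037. In closed form the excess is about 0.122p + 0.016p², which reaches 0.037 at p of about 29%. Under the smaller shifts even p = 50% gives only 0.014.

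**The case against.** The strongest reply is that Section 13.1 describes a setting and a cannula, not an order. Blood can be drawn in theatre before the first needle, and the Visit 1 text and Section 15 describe the cannula as placed in preparation for the biopsy. The rule in Section 5.1 is explicit, so a late draw would already depart from the protocol and fall under Section 17. The contrast with urine has an ordinary explanation: only blood can be taken through a cannula during a procedure, so only blood needed that option. The plasma aim in Section 2 concerns tumour DNA and progression, not every blood marker. The effect sizes above are assumed.

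Much of this stands. A reader might infer that some markers will be measured after needle trauma, or that the problem acts as a centre effect. The documents support neither: they say nothing about how often, where or in what order intraoperative draws occur. Nor does the illustration support saying that a real marker would be hidden, since an AUC of 0.75 that falls to about 0.70 is attenuated, not lost.

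The contradiction remains. Section 13.1 does not require the draw to precede the first pass, and Section 4 does not exclude a draw at the time of biopsy. The strict rule elsewhere does not cure this, because staff who follow Section 13.1 would have no reason to report a deviation. A Laboratory Manual that fixed the order would help in practice but would not remove the conflict within the protocol.

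**Conclusion.** The protocol contradicts itself on when research blood is drawn. As written, some samples could be taken after the first needle pass in compliance with Section 13.1, with no timing-based deviation trigger in Section 5.2. This bears directly on the pre-biopsy plasma aim in Section 2.

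The wording conflict is certain; its consequence is not. The size rests on three things absent from the documents: the share of post-needle draws, the existence and size of any needle effect, and whether that effect differs by cancer status. Of the three shares tried, only 50% gives a null marker a false signal beyond the 95% half-width of 0.037, and then only under the larger assumed shifts. It should be corrected because it touches a stated aim and costs little. It does not threaten the study as a whole and ranks below a must-fix.

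**What to change.** Reconcile Sections 4, 5.1 (the one-stop clinic text, the Visit 1 text and the note to Figure 2 and Table 1) and 13.1 so that a single rule governs the research draw, consistent with the protocol's own pre-biopsy aim. A cannula draw in theatre can stay as an option provided it precedes the first needle pass.

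Record on the eCRF whether the draw preceded the first pass, if this is not already captured. Treat a post-pass draw as a recorded deviation by adding timing to the triggers in Section 5.2. Flag such samples so that the circulating-biomarker analyses can be run without them. Flagging is preferable to compulsory exclusion: at the assumed shares of 10% to 50%, exclusion would remove 100 to 500 of the 1,000 men from those analyses.

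The cost is a few words in each section, one or two eCRF fields, a matching line in the Laboratory Manual, and possibly some samples set aside from the circulating-biomarker analyses. The rule concerns research sampling only.
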